**Figure 3 F3:**
[figure not shown]
Logic model of the Activity for Well-being program. RPE, Rating of Perceived Exertion; BREQ-3, Behavioural Regulations in Exercise Questionnaire-3; PNSE, Perceived Need Support in Exercise questionnaire; MARCA, Multimedia Activity Recall for Children and Adolescents (adult-version); ACSM, American College of Sports Medicine; AQOL-8D, Assessment of Quality of Life-8D; K-10, Kessler 10-item Psychological Distress Scale.

### Intervention mapping step 5: planning program adoption and implementation

#### Participants and research design

Participants will be self-selected from the population of frontline aged care workers, employed by the funding organisation. All participants will be recruited from the Adelaide metropolitan area and Fleurieu Peninsula, South Australia. Employees will be recruited via a generic email that will be sent out to all community-based support workers and care workers from participating residential sites. Expressions of interest will also be obtained through flyer drops and active promotion of the program at team meetings. This project will be undertaken using a mixed methods research design including a single-cohort, pre-post feasibility study, followed by a thorough process evaluation and qualitative evaluation of the program. Prior to commencing baseline testing, the researchers will obtain informed consent from each participant. Baseline testing will begin during the Australian late spring—early summer period and will be undertaken using a rolling recruitment until a sufficient number of participants have been enrolled in the program (~20–30 participants). Participants will complete a demographic questionnaire and undertake a pre-exercise screen using the Adult Pre-exercise Screening System (APSS) (97). The APSS is the Australian standard pre-exercise screening system that was developed as a collaboration between Exercise and Sports Science Australia, Fitness Australia and Sports Medicine Australia. Any participants who indicate previously diagnosed conditions, or signs/symptoms of cardiovascular disease in the first stage of the APSS will be required to obtain a medical clearance prior to undertaking exercise testing or program commencement. Participants will be included if they are 18 years of age or older, able to speak fluent English, currently employed as a frontline worker at the funding organisation and able to engage in moderate physical activity as defined by the American College of Sports Medicine (98). Ability to speak fluent English was placed as an inclusion criterion as many measures that will be used within this study are questionnaire-based and the lack of an ability to speak fluent English may impact the validity of these measures. Participants will receive an honorarium for undertaking the post-intervention and follow-up measures (a $25 and $50 gift card for these time-points, respectively). The honorarium will not be impacted by adherence to the intervention; these will be given for undertaking the measures only. As this is a feasibility study, sustainability of the program at an organisational level will not be addressed within the scope of this project; however, at an individual level the program was developed to promote long-term maintenance of behaviour change.

### Intervention mapping step 6: planning for evaluation

#### Process evaluation

##### Reach

Reach will be evaluated through a three-question online questionnaire that will be sent by email to all invited support workers and residential care workers at the end of the intervention period (after all participants have completed the active phase of the intervention). The survey will investigate the level of awareness of the program and the reasons why employees chose to participate in the study or not. As a part of the reach evaluation, baseline demographic data from program participants will also be compared to de-identified data of the whole target population to assess the representativeness of the sample. Data used for the evaluation of reach will be the mean (or median) age, proportion of males to females, and proportion of the sample based in each area (North, South, East, or West) or at each residential site.

##### Adoption

As the Activity for Well-being program has the support of higher-level management and it is expected the program will be adopted in all areas or sites that it is offered. Adoption will therefore be assessed as the level of perceived support of the program from implementing (i.e., management) staff. This will be evaluated by a seven-question, post-program, team leader survey. This short questionnaire will be sent to team leaders, site co-ordinators, and other implementation staff at the end of the intervention period and will survey the perceived aims, value, and observable impact of the program. It will also investigate the perceived barriers to and incentives for participation from the perspective of the implementing staff, and elements of maintenance at an organisational level (i.e., perceived value of maintaining a program such as this and intention to encourage the maintenance of healthy behaviours). Areas and sites that demonstrate high and low levels of perceived value and engagement with the program, type of service (i.e., residential or community), and geographical locations of sites and areas will be compared for differences in outcomes or recruitment numbers.

##### Fidelity

The fidelity of the implementation of the program (i.e., maintaining an autonomy supportive and collaborative approach) will be evaluated by audio-recording of a small number of randomly selected initial appointments. Recordings will be evaluated for fidelity by members of the research team who are not responsible for undertaking initial appointments with the participants, using a customised fidelity checklist. The checklist provides a score of “achieved” (1) or “not achieved” (0) for the fidelity of the interview based on three primary sections:
Were all components (goal setting, action and coping planning, pedometer, website, RPE/Feeling Scale/self-pacing) of the intervention explained to the participant appropriately?Was the activity plan developed collaboratively? (Used preferred activities; was perceived as achievable by the participant as measured on a 1–10 scale and adapted as necessary; and activities not imparted by the practitioner without participant engagement or consent).And, did the initial and total discussion adhere to the core principles of Motivational Interviewing? (expresses empathy; develops discrepancy between current behaviour and goals; roll with resistance; support self-efficacy; support autonomy).

Perceived autonomy support will be evaluated using the Health Care Climate Questionnaire (99) that will be sent out as an online survey, also managed by members of the research team who are not responsible for undertaking initial interviews.

##### Dose delivered and dose received

Detailed logs of support and communications for participants and information on website engagement will be kept and retrospectively evaluated for dose delivered and received. Dose delivered for physical activity and other program components (different methods for regulating activity intensity and different self-management tools) will be calculated from initial activity plans, and dose received will be scored using self-reported frequency of use from the Activity for Well-being Post-program Survey.

##### Context

The context of the environment in which the program is implemented will be evaluated through the post-program qualitative interviews. The participants will be purposefully selected to include participants with a diverse range of responses to questionnaires and differing outcomes. The interviews will explore factors that may have played a role in the effectiveness of the program (i.e., the perceived effectiveness of some tools or strategies over others, effectiveness of recruitment strategies, and general feedback about the program).

#### Evaluation of impact and outcomes

##### Behavioural outcome objectives—physical activity behavior

The behavioural outcome objectives for the Activity for Well-being project are to increase physical activity behaviour at 3 months and to maintain potential increases at 9 months post-intervention. Physical activity behaviour will be objectively measured using 7 day continuous accelerometry (GENEactiv, UK) at three time points (baseline, 3 months and 9 months). Two-day physical activity recall using the adult version of the Multimedia Activity Recall for Children and Adolescents (MARCA, Aus) will be used to assess changes in activity patterns and use of time between the three time points.

Esliger, Rowlands (100) demonstrated good validity (*r* = 0.97, *p* < 0.001), and intra- and inter-test reliability (Coefficient of Variation 1.8 and 2.4%, respectively) of GENEactiv accelerometers as measured using an Instron Multi-Axis Shaking Table. The authors also demonstrated that these accelerometers are comparable to portable gas analysis for measuring Metabolic Equivalents (METs) of activity achieving an area under the receiver operating characteristic curve (AUC) of 0.98, 0.91, and 0.91 during sedentary, moderate and vigorous, respectively, and high sensitivity and specificity for these activity categories (72–98%). The adult MARCA software has demonstrated good convergent validity for measuring physical activity levels (METs) compared to accelerometry, with Spearman coefficients (rho) at 0.72 (0.49–0.86), and very high test-retest reliability with intra-class correlation coefficients (ICCs) ranging from 0.99 to 1.00 (101).

##### Additional physical measures

Additional physical measures to be undertaken at each of the three time points will consist of a 6 min walk, body mass, resting blood pressure and heart rate. Height will be measured at baseline using a Tanita Leicester portable stadiometer. Body mass will be measured using a standard portable scale (Tanita UM-018). Resting blood pressure and heart rate will be measured on an Omran automatic blood pressure monitor (HEM-7121). The 6 min walk will be undertaken on a set walking course at each site. As data collection will need to occur across a number of different sites, the walking courses will vary between sites; however, where possible, the walk course for each individual will be kept consistent between time points (all courses ≥ 30 m in length). The 6 min walk will be undertaken according to the recommendations of the American Thoracic Society (102). The 6 min walk will be used to indicate change in physical capacity and to familiarise participants with the use of Borg's RPE scale (22) and Hardy and Rajeski's Feeling Scale (16). The 6 min walk has demonstrated high test-retest reliability (ICCs, 0.94–0.97) and although results were variable, the test has been positively correlated to other measures of exercise capacity (maximal oxygen consumption and maximum METs; r values ranging between 0.21 and 0.71) (103–105).

##### Well-being outcome objectives—psychological distress and quality of life

The well-being outcome objectives will be the improvement of psychological well-being at three-months, and maintenance of improvements at 9 months. Well-being will be measured using the Kessler 10-item Psychological Distress Scale (K-10) and the Assessment of Quality of Life-8D (AQoL-8 D) questionnaires. The K10 has demonstrated very good overall accuracy with an AUC of 0.90 (95% CI: 0.89 to 0.91) (106). In addition to strong validity data, the K10 has also demonstrated very good sensitivity and specificity for the identification of target disorders comparable to other measures such as the Global Health Questionnaire (GHQ) (106, 107). The AQoL-8D shows good internal consistency with Cronbach's alphas for the various dimensions ranging between 0.81 and 0.96, except for that of senses (Cronbach's alpha 0.52) (108, 109). The AQoL-8D has greater sensitivity than previous versions of the questionnaire in the domains of mental health (108).

##### Interpersonal environmental outcome objectives

The primary interpersonal environmental outcome objectives for the Activity for Well-being program are to increase perceived need-support at 3 months and maintain potential increases at 9 months through the use of a SDT -based approach. Perceived need-support will be measured via the Psychological Need Satisfaction in Exercise Scale (PNSE) which demonstrates good internal consistency with Cronbach's coefficient α ranging between 0.90 and 0.91 for all subscales, as tested in a population of undergraduate university students (110). The convergent validity of the PNSE compared to the subscales of Intrinsic Motivation Inventory and the Exercise Motivation Inventory-2 ranges between 0.32 and 0.65 and the discriminant validity ranges between-0.01 and 0.30 (110). Organisational environmental outcomes will be generally limited by the resources and scope of this trial.

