### Intervention mapping step 2: matrices of change objectives

The second step in the Intervention Mapping process involved the development of several matrices and a logic model to represent the health issue and the proposed methods of change. This step also involved selecting the target behavioural determinants (69). A number of specific behavioural determinants were identified both within the scientific literature and through the qualitative component of the needs assessment. The final changeable, target determinants were selected using a broader SDT-based approach which incorporated many of these specific determinants. The target behavioural determinants for the Activity for Well-being program included perceived autonomy, perceived competence, perceived relatedness, and positive exercise-related affect. Performance objectives were developed as “sub-behaviours” of the target behaviour. Three performance objectives were identified as important sub-behaviours for this population (find time to undertake physical activity, find motivation to undertake physical activity, and identify opportunities to undertake physical activity). Development of these performance objectives was informed by the qualitative component of the needs assessment. The resulting 12 change objectives were created as composites of the behavioural determinants and performance objectives. Incorporating information gathered from the needs assessment and the selected behavioural determinants, a logic model of the health issue was developed and is shown in Figure 1.

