#### Data processing and analysis

This project will use a variety of analytical methods, applying qualitative and quantitative techniques. The process evaluation will compare descriptive statistics of the sample population and groups within the sample to de-identified data from the support and care worker population from all participating sites and areas. Fidelity recordings of the sub-sample of initial interviews will be scored by members of the research team who are not responsible for undertaking initial interviews using a customised fidelity checklist. An overall score for each recording will be calculated as a proportion of the highest possible score, and descriptive statistics will be used to present overall fidelity of the initial interview sub-sample. Mean scores will be calculated for individual items on the HCCQ (inversing the score for item 13) to produce a mean score of overall autonomy support. Per protocol analysis will be undertaken using a random effects mixed-model to compare baseline, 3 month and 9 month time points for all well-being and behavioural outcome measures. Accelerometer data will be processed using the cut-points outlined by Esliger, Rowlands (100) to determine total minutes of sedentary, light, moderate and vigorous activity for each 7 day period of continuous accelerometry. Domain-specific means will be calculated for the PNSE and BREQ-3 and these will be analysed for differences in well-being or behavioural outcomes and movement between domains (i.e., movement toward more-self-determined types of motivation and increases in perceived support of psychological needs). Qualitative interviews undertaken with program participants and implementation staff will be audio recorded and transcribed. The transcripts will be coded by two independent researchers, and analysed using a structured thematic approach as described by Braun and Clarke (118). Conflicts will be resolved through discussion between the two researchers. A third researcher will be consulted in situations where conflicts cannot be resolved.

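### The need-support objective is measured with a scale named for need satisfaction, and the article gives that scale two different names

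*Protocol article*

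**What the plan says.** The section on interpersonal environmental outcome objectives states that the aims "are to increase perceived need-support at 3 months and maintain potential increases at 9 months". The next sentence names the instrument: "Perceived need-support will be measured via the Psychological Need Satisfaction in Exercise Scale (PNSE"). The same section gives its validity evidence: "The convergent validity of the PNSE compared to the subscales of Intrinsic Motivation Inventory and the Exercise Motivation Inventory-2 ranges between 0.32 and 0.65".

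The Figure 3 legend expands the abbreviation differently: "PNSE, Perceived Need Support in Exercise questionnaire".

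Data processing and analysis plans domain means for the PNSE and the BREQ-3. Among the movements to be looked for it lists "increases in perceived support of psychological needs". Since the other movement listed there concerns types of motivation, which is what the BREQ-3 covers, this phrase must describe the PNSE.

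A second instrument touches on support. Under Fidelity: "Perceived autonomy support will be evaluated using the Health Care Climate Questionnaire". The analysis section reduces it to one mean score of overall autonomy support.

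**The concern.** Need support is something the environment provides, here mainly the Exercise Physiologist and the program. Need satisfaction is a state of the participant, who feels autonomous, competent or connected to a greater or lesser degree. The first is meant to lead to the second, but either can move without the other.

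If the scale measures satisfaction and the result is reported as support, a gain with another source would be credited to the interpersonal environment. A participant who feels more competent after using a pedometer, setting goals or becoming fitter could score higher with no change in perceived support from anyone. The Discussion also expects the process measures to throw light on the mechanisms of change, and that requires knowing which of the two constructs was measured.

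**Working it through.** No arithmetic applies. The check sets the article's statements side by side.

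1. **Name of the instrument.** The outcome section calls the PNSE a need-satisfaction scale; the Figure 3 legend calls it a need-support questionnaire. These are two expansions of one abbreviation, and they name different constructs. They cannot both be right.

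2. **Objective against instrument.** Within the outcome section, the objective is support and the instrument is named for satisfaction. The analysis section carries the support reading forward. The label therefore runs through the objective, the legend and the interpretation, and is more than a slip in one place.

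3. **Which name the cited evidence favours.** The convergent coefficients of 0.32 to 0.65 are against two inventories that, by their names, concern a person's own motivation. No comparison with a measure of support from others is given. This fits a person-level construct better than an environmental one. It is indirect evidence, because the items are not shown.

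4. **Whether the article treats the two ideas as different.** Step 2 of the intervention mapping lists target determinants that "included perceived autonomy, perceived competence, perceived relatedness, and positive exercise-related affect". The first three are perceptions held by the participant. Step 4 describes support as what is delivered, and places support for relatedness chiefly in the relationship with the Exercise Physiologist. The Fidelity section uses perceived autonomy support in that environmental sense and gives it a separate instrument.

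5. **Where the constructs could part.** Step 4 gives 3 months of individualised support. Active follow-up by the Exercise Physiologist then stops, and help is available on request for a further 6 months (3 + 6 = 9 months). Newsletters and self-monitoring tools continue. Active practitioner support thus falls between the second and third measurements, while participants may go on feeling autonomous and competent. A stable 9-month PNSE score would be read as maintained need-support over a period in which active support had been withdrawn.

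6. **Whether another instrument answers the objective.** The Health Care Climate Questionnaire is described as covering autonomy support only, and its timing is not stated. Post-program survey questions and interviews address perceived program impact. None of these is described as measuring change in support for all the needs at baseline, 3 and 9 months.

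**The case against.** The best defence is that the article uses the word support loosely. The Introduction says that the basic needs must be supported for well-being, so perceived support of needs might simply mean needs being met. The article defines neither term and shows no items, and if the Figure 3 name is correct the construct matches the objective. This has some force: the mismatch rests on the scale's name and the cited validity evidence, not on its content. It does not remove the problem. If the legend is right, the outcome section names the wrong scale, so a correction is needed either way.

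It can also be said that the PNSE is a process measure in a single-cohort feasibility study of about 20 to 30 people, handled apart from the mixed model for the well-being and behavioural outcomes, and that the article already warns of limited conclusions on efficacy. That is fair, and it limits the weight of the point.

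Three stronger readings are tempting, and the article does not support them.

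- *One score serves as both cause and mediator.* The article never assigns the PNSE to the Step 2 determinants. The change objectives built from those determinants are evaluated by specific post-program survey questions, and the logic models are in figures that were not available.
- *Need support is never measured repeatedly.* The schedule of the Health Care Climate Questionnaire is unstated, and silence in a condensed article does not show a single administration.
- *The objective cannot be answered at all.* That questionnaire, the survey and the interviews each offer partial evidence on support.

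**Conclusion.** The point holds as an unresolved inconsistency of name and construct across the outcome section, the Figure 3 legend and the analysis section. Followed as written, the plan would report change in what is, by its name, a need-satisfaction score as change in perceived need-support.

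Its size is one objective, with its 3-month and 9-month results. The physical activity, K-10 and AQoL-8D outcomes and all data collection are unaffected. It deserves more than a clerical edit, because the label decides what may be concluded about the interpersonal environment, above all at 9 months.

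The conclusion assumes that the name in the outcome section is the right one, which the motivation-inventory evidence supports but does not prove. It should not be taken as established that any particular subscale is mislabelled: the article neither lists the subscales nor says how many there are.

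**What to change.** - Use one name for the PNSE throughout, including the Figure 3 legend.
- If it is the need-satisfaction scale, restate the objective as an increase in need satisfaction at 3 months, maintained at 9 months. Change the interpretation in Data processing and analysis to match, and do not report PNSE change as change in need support.
- If it is a need-support questionnaire, correct the name in the outcome section and confirm that the validity figures given there belong to that instrument.
- Report the Health Care Climate Questionnaire as the measure of perceived autonomy support from the practitioner.

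Both questionnaires are already planned, so the cost is wording, with no added burden on participants. The downside of the need-satisfaction wording is that the plan is left with no stated change objective for support across all the needs. If that change is truly wanted, a need-support instrument would have to be given at baseline, 3 and 9 months, which is a real addition to data collection.
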